**Methods:**

ARISE is a national, multicenter, non-inferiority randomized clinical trial. Two hundred patients with non-ST-segment elevation acute coronary syndrome will be randomized to either radial or femoral access using a vascular closure device. The primary outcome is the occurrence of vascular complications at an arterial puncture site 30 days after the procedure, including major bleeding, retroperitoneal hematoma, compartment syndrome, hematoma ≥ 5 cm, pseudoaneurysm, arterio-venous fistula, infection, limb ischemia, arterial occlusion, adjacent nerve injury or the need for vascular surgical repair.

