**Conclusions:**

The ARISE trial will help define the role of a vascular closure device as a bleeding avoidance strategy in patients with NSTEACS.

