##### Secondary outcomes

Individual components of the primary outcome, hematoma < 5 cm, major bleeding unrelated to the puncture site or myocardial revascularization surgery, device success and crossover rate; cardiovascular death, AMI or stroke at 12 months of evolution.

Study outcome definitions are listed in Table 1. A committee of clinicians will adjudicate all primary outcomes.

**Table 1 T1:** Outcome definitions

**Term**	**Definition**
Major bleeding	Type 3 ((3a) bleeding with hemoglobin drop ≥ 3 and < 5 g/dL, or packed red cells transfusion; (3b) bleeding with hemoglobin drop ≥ 5 g/dL, heart tamponade, bleeding requiring surgical intervention or bleeding requiring intravenous inotropic drugs; (3c) intracranial hemorrhage; subcategories confirmed by autopsy, imaging examinations or lumbar puncture; intraocular bleeding with vision impairment) or type 5 bleeding ((5a) possibly fatal bleeding, (5b) definitive fatal bleeding), according to the Bleeding Academic Research Consortium definition [30].
Retroperitoneal hematoma	Defined as building up of blood in the retroperitoneal space, caused by common femoral artery puncture above the inguinal ligament, not obtaining an adequate hemostasis with consequent hematoma formation. It is clinically manifested by dorsal, loin or inguinal pain, hypotension and/or hematocrit drop. Its diagnosis has to be confirmed by abdominal ultrasound and/or CT.
Compartment syndrome	Defined as abnormal tissue pressure increase inside an osteo-fascial compartment (considering in this analysis the involvement of upper or lower limbs after arterial puncture), impairing nervous and muscular structure irrigation, characterized by paresthesia, continuous pain, hypoesthesia, edema and stiffening of the affected region, peaking with tissue necrosis and/or permanent functional injury if not adequately treated.
Hematoma	Defined as localized collection of extravascular blood adjacent to the vessel, located in the topography of the punctured artery used to perform the procedure.
Pseudoaneurysm	Defined as a neocavity delimited by tissues adjacent to the injured vessel, fed by continuous blood flow into and out, coming from the real lumen through a narrow neck connecting it to the inside of the cavity. Diagnosis is determined by the presence of a pulsating bulge close to the puncture hole and is confirmed by duplex scanning.

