#### Statistical analysis

The primary analysis of the study is a non-inferiority comparison between the radial approach and femoral approach using VCD to decrease vascular complications at the arterial puncture site, in all randomized patients, based on the intention-to-treat principle.

Estimating a vascular complication rate pre-specified in the primary outcome of approximately 3% for the radial technique [19,32] and 12% for the femoral technique [26-31] and determining a non-inferiority margin of 0.15 based on historical data [18,19] with an alpha level of 0.05 and a beta level of 0.10, the minimum estimated sample size per group was established as 97 individuals. Twenty additional patients may be added to the final population to correct any subsequent loss of follow-up. This non-inferiority margin was derived from a trial that demonstrate the benefit of radial approach on the reduction of major vascular complications (hazard ratio, 0.37; 95% confidence interval, 0.27 to 0.52) as compared with femoral approach [18]. The non-inferiority margin of 0.15 was chosen in order to avoid a loss of greater than half the lower bound of the 95% confidence interval (0.27). The non-inferiority of the femoral approach with VCD will be declared if the lower confidence interval limit of 95% of the difference of both techniques does not include the specified inferiority margin value.

Categorical data will be presented as frequencies and group percentage and will be compared by chi-squared or Fisher’s exact tests. Continuous variables will be expressed as means and standard deviation and will be compared by Student’s *t-*test. Statistical analyses will be performed using Statistical Package for the Social Sciences for Windows (version 16.0; SPSS, Chicago, IL, USA).

The study was approved by the Dante Pazzanese Institute of Cardiology ethical committee, predicting and validating the Santa Casa de Marília as a co-participating institution. No extramural funding will be used to support this work. The authors are solely responsible for the design and conduct of this study, all study analyses and drafting and editing of the paper.

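### Component comparisons by chi-squared or Fisher tests say little about bleeding at this sample size; report risk differences with confidence intervals and pre-specify one puncture-site bleeding outcome

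*Protocol article*

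**What the plan says.** The Abstract's Conclusions read: "The ARISE trial will help define the role of a vascular closure device as a bleeding avoidance strategy in patients with NSTEACS". The main Conclusions section says nearly the same.

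The primary outcome (Methods, Primary outcome) is a composite of 11 kinds of puncture-site complication. Three are bleeding or hematoma: major bleeding, retroperitoneal hematoma, and hematoma of at least 5 cm. The others include arterial occlusion, symptomatic or not. Table 1 gives occlusion of the radial artery as its example of a silent occlusion.

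The components return under Secondary outcomes: "Individual components of the primary outcome, hematoma < 5 cm, major bleeding unrelated to the puncture site or myocardial revascularization surgery", followed by further items.

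Statistical analysis states one comparison for such data: "Categorical data will be presented as frequencies and group percentage and will be compared by chi-squared" or Fisher's exact tests. The only confidence-interval rule there is for the primary composite, against a margin of 0.15. On size, it says "the minimum estimated sample size per group was established as 97 individuals". The Abstract's Methods plan 200 patients in all. No power is claimed for any component.

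**The concern.** The question named in the Conclusions is bleeding, while the decision rule concerns a broader composite. Meeting a 15-point margin on the composite does not show that bleeding is similar in the two arms. A bleeding excess with the femoral approach can fit inside the margin, and silent radial occlusions count the other way.

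The reader must then look at the components. A test of difference suits that purpose poorly, because with about 100 per arm and rates of a few percent it will usually be non-significant whether or not an excess exists. Beside a non-inferiority result, such a p-value is easily taken as agreement. What is at stake is whether the report can say anything sound about bleeding.

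**Working it through.** **Starting point.** The article states no component power, so there is none to reproduce. I take the arm size as given: 97 (the stated minimum) or 100 (half of 200, assuming equal allocation). The 97 does not follow from its own inputs. With 3%, 12%, margin 0.15, one-sided 0.05 and 90% power, n = (1.645 + 1.282)² × (0.03×0.97 + 0.12×0.88) / (0.15 − 0.09)² = 8.57 × 0.1347 / 0.0036, or about 321 per arm. That is a separate matter and is not used below.

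**Rates assumed.** The article has no per-arm rate of access-site bleeding. Two stand-ins come from its Background:
- 1.4% versus 3.7%: radial versus femoral vascular complications in the cited 7,021-patient trial. This is a mixed set that includes large hematomas.
- 2% versus 5%: the ends of the range of major bleeding across trials, put in opposite arms by assumption.

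**Component power.** Power = Σ over (r, f) of Bin(r; n, p_radial) × Bin(f; n, p_femoral) × 1[p-value ≤ 0.05], summed exactly, two-sided. The article states no alpha for these tests, so 0.05 is assumed.

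| Radial v femoral | Fisher, n = 97 / 100 | Chi-squared (uncorrected), n = 97 / 100 |
|---|---|---|
| 1.4% v 3.7% | 4.9% / 5.3% | 15.2% / 15.6% |
| 2% v 5% | 9.0% / 9.6% | 18.1% / 18.6% |

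With 100 per arm, Fisher's test needs at least 6 femoral events against 0 radial, 8 against 1, or 10 against 2. At 1.4% and 3.7% the expected counts are 1.4 and 3.7. Power of 80% would need about 737 per arm at 1.4% versus 3.7%, or 588 at 2% versus 5%.

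**Can a bleeding excess sit inside a non-inferior composite?** Keep radial at the planned 3% (bleeding 1%, other 2%). Let femoral be 9% (bleeding 7%, other 2%), with no patient having both kinds. The split is assumed. I read the rule as: the upper 95% limit of femoral minus radial lies below 0.15.
- Hand check (Wald), n = 97: SE = √[(0.03×0.97 + 0.09×0.91)/97] = √(0.1110/97) = 0.0338. Then (0.15 − 0.06)/0.0338 − 1.96 = 0.70, and Φ(0.70) = 0.76.
- Exact sum, n = 97 to 100: non-inferiority is declared about 75% of the time by Wald and about 65% by Newcombe.
- Bleeding alone, 1% versus 7%: Fisher is significant 42 to 44% of the time, chi-squared 59 to 60%.

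**What an interval adds.** Take 0/97 radial and 5/97 femoral bleeds.
- Fisher: p = 2 × (97×96×95×94×93)/(194×193×192×191×190) = 0.059.
- Uncorrected chi-squared: 194×5/189 = 5.13, p = 0.023.
- Newcombe: the Wilson limits are 2.2% and 11.5% for 5/97, and 0 and 3.8% for 0/97. Lower limit = 5.15 − √[(5.15 − 2.2)² + 3.8²] ≈ 0.3 points. Upper limit = 5.15 + (11.5 − 5.15) = 11.5 points.

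The two tests that the plan allows fall on opposite sides of 0.05. The interval shows what the data allow: an excess anywhere from negligible to more than 11 points.

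**The case against.** Much can be said for the plan. Low power for single components is normal in a trial with a composite endpoint, and the article claims none. Frequencies and percentages will be shown, so 5 bleeds against 0 would be visible. The hypothesis and primary analysis concern vascular complications, and the bleeding sentence in the Conclusions is no decision rule. Smaller hematomas and bleeding away from the puncture site are also secondary outcomes. Some non-bleeding components, such as surgical repair or nerve injury from a hematoma, may rise together with bleeding and not offset it. Finally, this is a condensed article, and intervals for secondary outcomes may be in an analysis plan that is not shown.

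These points limit the matter to an improvement. They also rule out three stronger readings that a reader might infer:
- That the plan will report a bleeding excess as no difference. The article does not say so, and it rests non-inferiority on no component test.
- That power for bleeding is 5% at the document's own rates. The 1.4% versus 3.7% figures are not bleeding rates, and 5% applies to Fisher only; chi-squared gives about three times as much.
- That offsetting makes non-inferiority almost certain. An illustration with 9% in each arm (bleeding 1% v 7%, other 8% v 2%) is declared non-inferior 94 to 96% of the time, but it triples the planned radial rate of 3%. At 3% versus 9% the figure is about 75% by Wald.

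What stands is that the comparison for the components is stated and not merely left out. It is a poor way to inform the question that the Conclusions raise.

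**Conclusion.** The point holds as a cheap improvement. No stated figure is shown to be wrong by it. At 97 to 100 per arm, component tests have about 5 to 10% power by Fisher and 15 to 19% by chi-squared at the assumed rates, so a non-significant result is nearly uninformative and cannot back a non-inferiority claim. A sixfold difference in the composite's bleeding-type events (1% to 7%) would still pass the composite rule in roughly two-thirds to three-quarters of trials, depending on the interval method.

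This rests on two-sided 0.05 tests, equal arms, stand-in rates in place of the bleeding rates that the article lacks, and an assumed split of the composite. The conclusion is the same for both rate pairs tried.

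**What to change.** In Statistical analysis:
1. Report each component as a risk difference, femoral minus radial, with a Newcombe or Miettinen-Nurminen 95% interval, in place of a p-value.
2. Pre-specify one secondary outcome of puncture-site bleeding, meaning any of major bleeding, retroperitoneal hematoma, or hematoma of at least 5 cm, with its interval.
3. State that any conclusion on bleeding avoidance will rest on that interval and not on the composite alone. If the interval does not support it, state the result for vascular complications only.

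The cost is a few sentences and some table columns. The components are already collected, so no new data are needed. The downside is that the intervals will be wide and will show how little the trial says about single components.

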## Results and discussion

### Study status

Enrollment was initiated in September 2012, and until October 2013 91 patients were included. The inclusion phase is expected to last until the second half of 2014.

## Conclusions

Despite the proven efficacy of the radial approach in reducing vascular complications at the puncture site, the femoral approach remains the preferred technique at many centers worldwide. The ARISE trial will help define the role of vascular closure devices as a bleeding avoidance strategy in patients with NSTEACS.

## Abbreviations

ACS: Acute coronary syndrome; AMI: Acute myocardial infarction; ECG: Electrocardiogram; GPI: IIb-IIIa glycoprotein receptor inhibitor; NSTEACS: Non-ST-segment elevation acute coronary syndrome; PCI: Percutaneous coronary intervention; TIMI: Thrombosis in myocardial infarction; UFH: Unfractionated heparin; VCD: Vascular closure devices.
